## Abstract

**Background:**

The sectorization of health-care systems leads to inefficient treatment, especially for elderly people with cognitive impairment. The transition from hospital care to primary care is insufficiently coordinated, and communication between health-care providers is often lacking. Consequences include a further deterioration of health, higher rates of hospital readmissions, and institutionalization. Models of collaborative care have shown their efficacy in primary care by improving patient-related outcomes. The main goal of this trial is to compare the effectiveness of a collaborative care model with usual care for people with cognitive impairment who have been admitted to a hospital for treatment due to a somatic illness. The aim of the intervention is to improve the continuity of treatment and care across the transition between the in-hospital and adjoining primary care sectors.

**Methods/design:**

The trial is a longitudinal multisite randomized controlled trial with two arms (care as usual and intersectoral care management). Inclusion criteria at the time of hospital admission due to a somatic illness are age 70+ years, cognitive impairment (Mini Mental State Examination, MMSE ≤26), living at home, and written informed consent. Each participant will have a baseline assessment at the hospital and two follow-up assessments at home (3 and 12 months after discharge). The estimated sample size is *n* = 398 people with cognitive inmpairement plus their respective informal caregivers (where available).

In the intersectoral care management group, specialized care managers will develop, implement, and monitor individualized treatment and care based on comprehensive assessments of the unmet needs of the patients and their informal caregivers. These assessments will occur at the hospital and in participants’ homes. Primary outcomes are (1) activities of daily living, (2) readmission to the hospital, and (3) institutionalization. Secondary outcomes include (a) frailty, (b) delirium, (c) quality of life, (d) cognitive status, (e) behavioral and psychological symptoms of dementia, (f) utilization of services, and (g) informal caregiver burden.

**Discussion:**

In the event of proving efficacy, this trial will deliver a proof of concept for implementation into routine care. The cost-effectiveness analyses as well as an independent process evaluation will increase the likelihood of meeting this goal. The trial will enable an in-depth analysis of mediating and moderating effects for different health outcomes at the interface between hospital care and primary care. By highlighting treatment and care, the study will provide insights into unmet needs at the time of hospital admission, and the opportunities and barriers to meeting those needs during the hospital stay and after discharge.

**Trial registration:**

ClinicalTrials.gov, NCT03359408; December 2, 2017.

**Electronic supplementary material:**

The online version of this article (10.1186/s13063-019-3636-5) contains supplementary material, which is available to authorized users.

## Background

The German health-care system is strongly sectorized with (a) outpatient treatment and care predominantly provided by general practitioners (GPs) and specialists in private practice, (b) inpatient treatment and care provided in hospitals, and (c) rehabilitation. While treatment and care within each of these sectors is generally of high quality, there is often a challenge to deliver continuous treatment and care across these sectors. Treatment pathways for people with chronic diseases or elderly people suffering from multiple morbidities and cognitive impairment often include frequent transitions between these sectors. However, in Germany, the boundaries between sectors are often rigid, rendering transitions between sectors a threat to treatment continuity and care coordination, which often results in unfavorable outcomes for patients. After this problem was identified and described in detail by the Advisory Council on the Assessment of Developments in the Health Care System in 2012 [1], a number of different remedies were proposed. Their impact, however, has been limited to date. This study addresses the lack of integrated cross-sectoral approaches to the challenges caused by the sectorization of the German health-care system.

In particular, there is a lack of sustainable management at the interface between in- and outpatient treatment. Treatment and care need to be oriented more toward the patients’ needs rather than the hospitals’ processes or the needs of specific diseases [2, 3]. There is evidence that patient involvement is positively associated with improved health behavior and treatment outcomes [4, 5]. In Germany, some discharge management is mandatory by law and must be available in each hospital [6]. It is financed by statutory health insurance and has just recently been specified and extended [7, 8]. However, the discharge management in routine care differs considerably from the expert standard proposed by, for example, the German Network for Quality Development in Nursing [9]. There should be more emphasis on an individualized needs assessment, continued care after discharge, and, most importantly, the inclusion of informal caregivers or relatives in the discharge process. For elderly people with cognitive impairment (PCI) in particular, it is well known that they have an increased need for professional and informal care at home. However, caregiving is burdensome [10, 11], and as such, informal caregivers require attention and support from health-care providers. Reducing the burden on caregivers is not only beneficial to the caregiver but also to the patient and—from a societal perspective—to the health-care system.

Current figures indicate that elderly people visit emergency units in hospitals more often than younger people do. In addition to their somatic illness, many of these elderly patients also face mental health problems. Approximately 50% of them have cognitive impairment, 27% suffer from delirium, 8–32% suffer from depressive symptoms, 21% suffer from apathy, and 9% suffer from agitation, aggression, or other symptoms [12]. In general, approximately half of the patients in hospitals are older than 65 years [13]. However, cognitive impairment is significantly underdiagnosed in hospitals. According to the German Federal Health Reporting Database (www.gbe-bund.de), 19,632,764 patients were treated in hospitals in Germany in 2014. Only 0.002% had a diagnosis of dementia [14]. However, an international review of dementia research suggests that prevalence rates range from 3.4% to 43.3%, depending on the age composition, study design, the setting, and the identification and screening criteria [15]. A nationwide survey of 1844 head nurses yielded an average point prevalence of 23% of PCI, independent of the specialty of the ward [16]. Accordingly, official data from the German Federal Health Reporting Database (www.gbe-bund.de) seem to underestimate the number of PCI and, consequently, the associated challenges for PCI, their informal caregivers, and the primary health-care providers. Current German primary data indicate that the point prevalence of PCI is close to 20% based on a screening test [17]. The point prevalence of dementing illnesses in German hospitals has been reported to be 18.4%. Delirium, most often due to dementia, was present in 5.1%. Only 60.0% had no cognitive impairment [18].

It is well established that cognitive impairment and the resulting behavioral and psychiatric symptoms pose a challenge for (a) the patient, relatives, and informal caregivers, (b) the treatment of the patient, (c) the hospital team caring for the patient and (d) the hospital setting in general. The behavioral and psychological symptoms of dementia are common in older PCI in hospitals and are associated with considerable distress in the nursing staff [19]. Admission to hospital is associated with cognitive problems or worsening of pre-existing cognitive problems, which increase the risk for readmission, institutionalization, and mortality [20–22]. These risks are aggravated by factors such as comorbidities, malnutrition, activities of daily living (ADL), depression, and other mental disorders.

Upon discharge from the hospital, these risks complicate the transition to primary care and increase the need for post-discharge support for patients living in their homes. However, the specific needs of these patients are not adequately addressed in Germany today: (a) postoperative treatment (by outpatient practitioners and therapists) and care arrangements are not sufficiently coordinated, (b) medical reports and patient data necessary for the continuation of treatment and care are communicated incompletely or delayed between hospitals and GPs, and (c) guidelines for intersectoral clinical pathways do not exist. These structural deficits, in summary, lead to insufficient treatment and care for many elderly PCI, cost-intensive unscheduled rehospitalizations, and premature institutionalization. Ultimately, both patients and health-care providers are often dissatisfied.

From a patient-centered perspective, one approach to overcoming these interface problems is collaborative case and care management. In Germany, the DelpHi-MV study (Dementia: Life- and Person-centred Help in Mecklenburg-Western Pomerania) [23, 24] tested the efficacy of a model of collaborative care of patients with dementia living in their own homes. The DelpHi-MV study is a GP-based cluster-randomized controlled intervention trial in primary-care settings that evaluated the efficacy of dementia care management [23]. The DelpHi-MV intervention improved relevant patient- and informal-caregiver-related outcomes [24]. Compared with care, the usual behavioral and psychiatric symptoms of dementia and informal caregiver burden were significantly decreased. Moreover, in the subgroup of patients who did not live alone, their quality of life increased. Patients with dementia receiving DelpHi care management had an increased chance of receiving antidementia drug treatment.

In a separate acceptance study, approximately 80% of the participating GPs indicated that care management as provided in the DelpHi-MV study should become a basic service in routine care [25]. Its further development for application in an intersectoral setting seems promising, since the intervention modules are well defined, the necessary qualification for the dementia care managers has been developed [26, 27], and a computerized intervention management tool has been programmed [28]. It is based on the principles of (i) individualized needs assessment, (ii) computer-supported development of a modular treatment and care plan, and (iii) implementation of this plan and the monitoring of its practicability and acceptance.

Based on the DelpHi experience, the objective of the Intersec-CM interventional trial is to test the efficacy of intersectoral care management for PCI around the time of discharge from the hospital back into primary care. The main hypotheses are as follows:
PCI receiving intersectoral care management during the transition from hospital to their homes and into primary care will have better patient-oriented health outcomes than PCI receiving care as usual (CAU) at 3 and 12 months after discharge.PCI receiving intersectoral care management during the transition from hospital to home will have a lower frequency of unscheduled readmissions to hospital than PCI receiving CAU.PCI receiving intersectoral care management during the transition from hospital to home are less likely to be institutionalized 12 months after discharge from hospital than PCI receiving CAU.

## Methods/design

### Study design and sites

This study is a multisite longitudinal randomized controlled intervention trial with two arms (intervention and CAU) and four time points of data assessment (screening, baseline, follow-up 1, and follow-up 2). The aim is to compare the effectiveness of an intervention (intersectoral care management designed to improve health and social outcomes of PCI in inpatient and ambulatory care) with CAU. Two hospitals are participating in this trial, the Evangelisches Klinikum Bethel in Bielefeld, North Rhine-Westphalia, and Greifswald Medical School, Mecklenburg-Western-Pomerania, with sites in Wolgast and Greifswald. The first patient was enrolled on 1 November 2018. Recruitment is planned for 12 months; thus, the last patient is expected to be enrolled on 31 October 2019. We expect the last follow-up assessment 13 months later, on 30 November 2020. The design of the study is summarized in Fig. 1. Ethical approval for this trial has been obtained from the ethics committee of Greifswald Medical School (registry number: BB 159/17) and the ethics committee of the Chamber of Physicians of Westphalia-Lippe (registry number: 2017–688-b-S). The trial is registered at ClinicalTrials.gov (NCT03359408).

**Fig. 1 Fig1:**
[figure not shown]
Flow chart for the intersec-CM trial. MMSE Mini Mental State Examination

### Study population and selection criteria

Elderly PCI admitted to a general hospital with somatic illnesses are eligible for the study. The inclusion criteria for these index participants were as follows: age 70+ with cognitive impairment detected with a standardized screening instrument (Mini Mental State Examination, MMSE ≤ 26) [29], having lived at home prior to the index admission, living in the catchment area of the hospital, and providing written informed consent (personally or by their legal guardian when necessary). The exclusion criteria are acute stroke as the primary reason for admission, terminal disease, or insufficient language skills.

Since the treatment and care of elderly PCI may be dependent on informal caregivers, index participants are asked to name their informal caregivers (e.g., a spouse, child, or friend). The informal caregiver is then invited as an independent study participant upon provision of written informed consent. While we put effort into recruiting this group, the participation of an informal caregiver is not a necessary requirement for the inclusion of the index participant.

### Intervention

The framework for the intervention is evidence-based dementia care management as conducted in the DelpHi-MV study [23, 24]. In principle, it consists of (i) a comprehensive assessment of the health and social status of the patient at the time of their admission to the hospital, (ii) a comprehensive needs assessment at the time of their admission to the hospital or shortly after, (iii) if applicable and available, an assessment of their informal caregiver’s health and burden, (iv) systematic written feedback to the treating hospital physician and nursing staff with recommendations for treatment and care for the patient after discharge (hospital information letter; these recommendations are based on predefined algorithms using the results of the assessment), (v) an assessment of the patient’s health at the time of discharge, (vi) a comprehensive needs assessment at the patient’s home immediately after discharge, (vii) if applicable and available, an assessment of the informal caregiver’s health and burden at the patient´s home, and (viii) support in meeting the patient’s needs as identified by the assessment.

The entire intervention delivery by specifically trained study nurses (case manager, social worker, or dementia care manager) [30] will be supported by a computerized tablet-based intervention management system for intersectoral care management. The system is a rule-based expert decision support system that matches individual patient characteristics to recommendations for treatment and care. The system supports the identification of a patient’s unmet needs, selects corresponding patient-specific interventions, and integrates these into an individualized intervention plan. The intervention management system has been proven to support the systematic identification of unmet needs, to improve the selection of specific intervention modules, and to address them systematically [25, 28].

The intervention used in this study does not, however, replace any provisions offered by other providers in the hospital or in ambulatory settings.

### Outcomes

The primary objective of the study is to evaluate the efficacy of intersectoral care management for elderly PCI admitted to hospital. Primary outcomes are ADL (which are a proxy for functionality after discharge), unscheduled readmissions, and premature institutionalization.

They are measured as follows:
*Activities of daily living* will be assessed using the Bayer Activities of Daily Living Scale (B-ADL) [31], which consists of 25 items on everyday problems and challenges. The questionnaire targets community-dwelling patients who suffer mild cognitive impairment or mild-to-moderate dementia. It assesses the patient’s competence with general ADL and specific tasks in everyday life in the following domains: medication, hygiene, reading, conversation, telephoning, shopping, food preparation, handling money and financial affairs, using household appliances, transportation, leisure activities, everyday tasks that require unimpaired short- or long-term memory, and orientation in familiar and unfamiliar surroundings. The B-ADL also assesses nonspecific tasks requiring cognitive functions for the management of everyday life. These include remembering where to continue with an ongoing task after an interruption, doing two things at the same time, coping with unfamiliar or new situations that require the processing of new information, as well as the safety aspects of ADL and difficulties performing a task when under pressure.To assess *readmissions to hospital*, each participant will be asked how many times they have been hospitalized (unplanned and planned) within the last 12 months. This is one item in the Questionnaire on the Use of Medical and Non-Medical Services in Old Age (FIMA) [32], which is administered to assess utilization of health services. FIMA examines socioeconomic variables and other medical factors to determine health-related costs.*Institutionalization* will be assessed during the study, since the participants’ living situation will be checked at each assessment.

The secondary outcomes of this trial are not explicitly targeted by the intervention but were chosen as important moderating or mediating factors. Among those, we consider the following: (a) frailty, (b) delirium, (c) quality of life, (d) cognitive status, (e) neuropsychiatric symptoms, (f) utilization of health services, and (g) informal caregiver burden. We assume that (a), (b), and (f) are moderating factors and that (c), (d), (e), and (g) are mediating factors.
Frailty will be measured using the Edmonton Frail Scale [33]. This is a reliable tool in geriatric medicine for assessing the frailty of older patients on the domains of cognition, general health status, functional independence, social support, medication use, nutrition, mood, continence and functional performance. Scores can range from 0 (not frail) to 17 (severe frailty).Delirium will be assessed using the Family Confusion Assessment Method [34]. It consists of up to seven items inquiring about the presence of different delirium-specific symptoms (yes or no) and one item about general mental health since the last visit (better, worse, or about the same). More information regarding the occurrence, stability, duration, frequency, and recency are asked when a symptom has been reported as present. An algorithm published by the developers is used to calculate a score for suggested delirium to be present (1) or not (0). This tool is a screening instrument and is not intended to provide a clinical diagnosis. Due to the economic and time constraints of this study, a detailed, guideline-oriented diagnosis of delirium will not be made.Quality of life of the PCI will be assessed using the five-dimension EuroQol Questionnaire for both the PCI and the caregiver [35]. This is a standardized instrument developed by the EuroQol Group to provide a simple generic measure of health in clinical and economic appraisals. Scores range from 0 (death) to 1 (best possible health).Cognitive status will be assessed using the MMSE [29]. This is a 30-point questionnaire designed to measure cognitive impairment. The questions are grouped into seven categories, each representing a different cognitive domain or function: orientation to time (5 points), orientation to place (5 points), registration of three words (3 points), attention and calculation (5 points), recall of three words (3 points), language (8 points), and visual construction (1 point). Scores range from 0 (lowest cognitive status) to 30 (cognitive status not impaired).Neuropsychiatric symptoms will be assessed using the Neuropsychiatric Inventory [36]. This is assessed using interview of the caregiver (when available) on 12 dimensions of neuropsychiatric behavior: delusions, hallucinations, agitation, dysphoria, anxiety, apathy, irritability, euphoria, disinhibition, aberrant motor behavior, night-time behavior disturbances, and appetite and eating abnormalities. Scores range from 0 (no neuropsychiatric symptoms) to 144 (severe symptoms, very often in all 12 dimensions).The utilization of health services will be assessed using the Resource Utilisation in Dementia Questionnaire [37] and FIMA [32]. The former will be used to assess the provision of informal care as well as the informal caregivers’ productivity losses. FIMA assesses the frequency of the utilization of medical and formal care services. Scores indicate whether a service is used (1) or not (0).Informal caregiver burden will be assessed using the seven-item (short) version of the Zarit Burden Inventory [38]. This is a caregiver self-report measure that examines the burden of caring associated with functional and behavioral impairments in social, psychological, and physiological contexts and at home. Scores range from 0 (no burden) to 28 (highest possible burden)

The data assessment tools for these dimensions will be chosen either based on their recommendation by the expert group of the Joint Programme Neurodegenerative Disease or because they are in common use in larger German trials such as IDEMUCK [39], DelpHi-MV [23, 40, 41], DemNet-D [42–45], and IDA [46]. These instruments have been validated, which will guarantee the validity of the results and comparability with German and international studies. An overview of the assessment points of the outcome measures is provided in Fig. 2.

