### Data collection

Specially trained study staff will collect the data needed for the trial in computer-assisted face-to-face interviews and from patient records. All interviews will be standardized using validated and reliable questionnaires. To reduce interviewer bias, study staff will be retrained and supervised weekly to ensure the optimum degree of comparability. The source of information in the interviews will predominantly be the participant with cognitive impairment. However, due to the cognitive impairment, the validity of the information obtained may be compromised. The informal caregiver—if available—will validate facts (such as sociodemographic status and ADL) and fill in gaps in the patient’s answers. The source of each data item will be documented and controlled for.

Data will be stored on a tablet-based computer at the time of assessment. This allows for plausibility checks at the time of assessment and will avoid the errors that would otherwise result from transferring the data from written paper notes to a computer. Data collection will take place in the hospital (at screening and at baseline) and at the participants’ home (at the first and second follow-ups).

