### Limitations

There are several limitations of this trial, which might be a threat to the reliability, validity, or generalizability of the results.
All subjects in the study are staying in hospital due to an acute illness or planned treatment that is not necessarily associated or connected with cognitive impairment. This causes heterogeneity in the index illnesses, which might decrease comparability between subjects. However, there is an objective, reliable, and valid inclusion criteria for each participant, so that conclusions can be drawn for this sample. Also, the study is a close-to-routine-care trial and since the complex intervention aims at the whole health-care situation with consideration of comorbidity, this will not decrease the usefulness of our results.Adherence to the study protocol might be difficult because the trial is conducted in routine care rather than in an experimental setting. This is a trade-off between evaluating the effect purely due to the intervention and the effect under close-to-routine conditions. We chose the second aim since it raises the chances of and gives more guidance to the implementation (if the intervention is successful).Cognitive impairment might decrease the validity of the information given by the participants. However, some measures (e.g., quality of life) must be provided directly by the participant, since they are subjective. Other information can and will be checked by the study assistants, dependent on the cognitive status of the participant (like demographic data). We do include caregivers in the study and access patient records to achieve the best possible valid information. Furthermore, we will include cognitive status as a mediating factor in our analyses.

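### The only stated measure of the readmission primary outcome is a 12-month recall item answered mainly by people enrolled for cognitive impairment; no hospital-record check is tied to it

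*Protocol article*

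**What the plan says.** The Outcomes section lists the primary outcomes: "Primary outcomes are ADL (which are a proxy for functionality after discharge), unscheduled readmissions, and premature institutionalization". For readmission it names one measure, a single item of the FIMA service-use questionnaire: "each participant will be asked how many times they have been hospitalized (unplanned and planned) within the last 12 months".

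The people answering are selected under Study population and selection criteria: "age 70+ with cognitive impairment detected with a standardized screening instrument (Mini Mental State Examination, MMSE ≤ 26". The same section requires "living in the catchment area of the hospital" and makes a caregiver's participation optional.

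Data collection names the informant: "The source of information in the interviews will predominantly be the participant with cognitive impairment". It adds that "due to the cognitive impairment, the validity of the information obtained may be compromised". An available caregiver "will validate facts (such as sociodemographic status and ADL) and fill in gaps in the patient’s answers". The section opens by giving patient records as a second data source besides interviews, without saying for which items, and it places follow-up data collection in the home. Limitations says: "We do include caregivers in the study and access patient records to achieve the best possible valid information". The specific record uses described under Study procedure are the baseline content (sociodemographic data, diagnoses, medication history) and the documentation of medical status at discharge.

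Sample size expects about 30% loss to follow-up, leaving 279 complete at 12 months. Statistical analysis imputes missing follow-up values by chained equations within study group and uses a logistic model for readmission.

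**The concern.** A count of hospital stays over a year is a demanding recall task, and this population was recruited because its cognition is impaired. The protocol recognises the problem in general terms but attaches no remedy to this outcome. A caregiver exists for only some participants and can fill a visible gap, but a stay that the participant has simply forgotten need not show up as a gap.

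Three things are at stake. Misclassification unrelated to arm pulls the group difference towards zero and costs power. Misclassification that differs by arm biases the estimate, and more participants would not cure that; it is possible here because participants and staff know the allocation once the intervention has started, and only one arm has post-discharge contact with care managers. Finally, whatever happens after a participant's last completed interview goes unobserved, although a hospital record of it may exist.

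The participating hospitals should hold dates and admission type for stays in their own wards. Those two items would also separate unscheduled from planned stays, which the named outcome requires.

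**Working it through.** **1. The plan's own figure.** Sample size gives 199 per arm for ADL at d = 0.25, alpha 0.05 and 80% power. One-sided: n = 2(1.645 + 0.842)²/0.25² = 197.8, so 198 by the normal approximation; the t-test gives 198.5, so 199. The figure reproduces as a one-sided calculation at the full 5%. It concerns ADL only. No event rate, effect or power is stated for readmission, so nothing below contradicts a stated figure.

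**2. Loss to follow-up.** 398 × 0.70 = 278.6, the 279 stated. 398 − 279 = 119 participants would have no 12-month answer.

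**3. Recall error equal in both arms (illustration).** Assumed, not from the documents: true 12-month risks of 40% (usual care) and 28% (intervention), and the sensitivities and specificities below. From the plan: 199 per arm, one-sided 5%. Dropout and the Holm step are left out.

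Observed risk = sens × p + (1 − spec) × (1 − p). Power = Φ(difference/SE − 1.645), with SE = √[p₁(1−p₁)/n + p₂(1−p₂)/n].

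| Sensitivity | Observed risks, spec 100% | Power | Observed risks, spec 95% | Power |
|---|---|---|---|---|
| 100% | 40.0% vs 28.0% | 82% | – | – |
| 90% | 36.0% vs 25.2% | 76% | 39.0% vs 28.8% | 70% |
| 75% | 30.0% vs 21.0% | 66% | 33.0% vs 24.6% | 58% |
| 60% | 24.0% vs 16.8% | 56% | 27.0% vs 20.4% | 46% |

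First row: SE = √(0.24/199 + 0.2016/199) = 0.0471; 0.12/0.0471 = 2.547; Φ(2.547 − 1.645) = 0.82.

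**4. Other assumed risks.** With perfect specificity, 199 per arm, one-sided 5% and a pooled null variance, moving from complete capture to 80% sensitivity changes power from 64% to 51% (50% vs 40%), from 92% to 81% (50% vs 35%) and from 67% to 55% (40% vs 30%). The loss is 11 to 13 points in each case.

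**5. Dropout and multiplicity.** For 40% vs 28% with perfect recall, 139 per arm and the first Holm step (0.05/3 = 0.0167), power is 50%. The 82% is a reference point for the comparison, not this trial's power.

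**6. Recall that differs by arm (illustration).** With sensitivity of 70% in usual care and 80% in the intervention arm, a true 40% vs 30% appears as 0.70 × 40% = 28% vs 0.80 × 30% = 24%, so a benefit shrinks. With equal true risks the apparent risk ratio is 0.80/0.70 = 1.14. With the sensitivities reversed it is 0.70/0.80 = 0.88, an apparent benefit where none exists. The documents do not say which direction applies.

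**The case against.** The protocol does more than ask the participant. Data collection lists patient records as a source without limiting them to baseline, and says that the source of each item is documented and controlled for. Limitations says that study assistants will check other information depending on cognitive status. The caregiver examples are only examples, and filling gaps can include service-use answers. This stands against any claim that records are confined to baseline or that caregivers are barred from this item. It does not close the gap, because none of these statements names readmission or a follow-up record review.

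Several stronger readings are tempting and should not be drawn:

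- *Most readmissions are in the study hospitals' records.* This would be inferred from the catchment criterion alone. No share is given, and stays elsewhere are possible.
- *Readmissions are under-reported.* This is likely, but no recall accuracy is given.
- *The outcome is lost with every dropout.* A 3-month interview comes first, people lost to follow-up are recontacted where possible, and missing values are imputed. Imputation does not recover actual events, but the outcome is not simply discarded.
- *Better recall in the intervention arm hides a benefit.* The legend to Fig. 2 shows the last intervention phase ending 3 months after discharge, well before the 12-month interview. The opposite pattern is equally conceivable.

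The remedy also has a weakness. Combining records for all with recall for other hospitals makes capture depend partly on being interviewed, and the share of stays elsewhere may differ between sites.

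**Conclusion.** The concern holds in a limited form. Followed as written, the plan measures a primary outcome by one recall item from informants whose reliability it questions itself, and it ties no independent check to that item. Misclassification is likely. Its amount, and any difference between arms, cannot be derived from the document.

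Under the assumed 40% vs 28% with perfect specificity, the loss is about 6 power points at 90% sensitivity, 15 at 75% and 26 at 60%; imperfect specificity adds to it. These figures rest on assumed risks and accuracies, full alpha and no dropout, so they show how sensitive the outcome is to recall and do not forecast the trial's power. About 119 participants would also have imputed, not observed, readmission status at 12 months. This is a design improvement that should be made; it is not an error in a stated figure.

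**What to change.** In Outcomes and Data collection, state that readmissions are ascertained for every randomized participant, where consent allows, from the participating hospitals' admission records: dates and emergency or planned status, from index discharge to 12 months, extracted in the same way in both arms. This includes participants who die or miss an interview. Keep the FIMA answer, from participant or caregiver, to add stays in other hospitals. Report agreement between records and recall by arm.

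Because stays elsewhere are captured only in those interviewed, add a sensitivity analysis restricted to readmissions to the study hospitals.

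The cost is one data extract per hospital at the end of follow-up and a check that consent covers it; hospital records are already used at baseline. Stays elsewhere still depend on recall, and some participants who withdraw may have to be excluded. Trials status reports 236 of 398 enrolled by 22 July 2019, and Study design and sites expects the last follow-up on 30 November 2020, so on the plan's own dates the change could be made before follow-up ends.
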